### Data analyses

2.9

#### Calculation of power and sample size

2.9.1

*For depressive symptoms,* Cooney et al. (2013) report a large effect size of −1.22 (−2.21, −0.23) in favor for exercise plus treatment versus treatment, and a medium effect size for all control conditions with *d* = −0.62. For the subgroup of light/moderate activity interventions, they report an also large effect size of −0.83 (−1.32, −0.34). Therefore, we also expect a medium effect size in the MADRS between both groups at discharge. *For PA,* Heinzel et al. (2015) find an effect size of *d* = −0.49 (95% CI −0.91 to −0.06, *Z* = 2.23, *p* = 0.03) in favor of exercise for body functioning/fitness indicators in five trials of their meta‐analysis. Thus, we expect a small but close to moderate effect size for PA difference at discharge.

Taken together, we assume a small to moderate effect size for the group difference. According to Cohen (1988), *f*
^2^ = 0.02 and *f*
^2^ = 0.15 represent small and moderate effect sizes, respectively. Conservatively, we aim to detect a small effect of *f*
^2^ = 0.06. For this, in a parallel group, fixed sample trial with a multivariate analysis of variance (MANOVA; 5% significance level with a power of 95%) a sample size of 262 is necessary (using G*Power Version 3.2.1). F. B. Schuch et al. (2016) find a dropout rate of 17.2% in their meta‐analysis for depressed patients in exercise studies. Assuming a possible additional loss of 17% through overall missing data that is seen in studies using accelerometers (Helgadóttir et al., 2017), the sample size is enlarged to be 396, for practical reasons rounded up to 400 (40 per participating center, enables 34% of data loss by dropout or missing data).

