#### Combination treatment

1.4.2

More research on combination treatments with TAU and TAU + exercise is needed because present findings are not clear concerning the effect size, so far (it has a range of *g* = −0.68 to *g* = −0.08; Kvam et al., 2016). This is mostly due to differences in methodology of the studies and in program variables of the exercise interventions. The effect of exercise decreases with blinded outcome, intent‐to‐treat‐analysis and when compared to guideline TAU.

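### The 95% power holds for f² = 0.06, three times the protocol's own small effect; for its small value of f² = 0.02 power is about 52%

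*Protocol article*

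**What the plan says.** All of this is in the protocol article, section 2.9.1 (Calculation of power and sample size).

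- **Expected effects.** For depression the section cites several literature values, among them d = −0.62 over all control conditions, and expects a medium effect on the MADRS. For physical activity (PA) it cites d = −0.49 and concludes: "Thus, we expect a small but close to moderate effect size for PA difference at discharge".
- **Summary.** Taking the two together, "we assume a small to moderate effect size for the group difference".
- **Scale.** It then gives two anchors, stating that f² = 0.02 and f² = 0.15 "represent small and moderate effect sizes, respectively".
- **Target.** The next sentence reads "Conservatively, we aim to detect a small effect of" f² = 0.06.
- **Size.** For a MANOVA ("5% significance level with a power of 95" per cent) it requires 262 patients, enlarged to 396 and rounded to 400 to allow for 34% loss.

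**The concern.** The scale and the target stand in adjacent sentences and do not agree. The value labelled small is three times the value given as small one sentence before. A reader who takes the label at face value will believe that the trial had 95% power for a small effect, conservatively chosen.

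This bears on how a null result would be read. The protocol treats small effects as both plausible and worthwhile. Section 1.4.2 (Combination treatment) reports add-on effects from g = −0.68 to g = −0.08 and says: "The effect of exercise decreases with blinded outcome". MADRS raters are blinded in this trial. Section 1.4.5 argues that even a mild gain could matter to a patient. If power for a small effect is near one half, a non-significant MANOVA says little about whether such an effect exists.

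**Working it through.** **Inputs from the article.** Two groups, 1:1 (2.4.1); two primary outcomes, depression and PA, tested by MANOVA (2.9.2); α = 0.05, power 0.95, f² = 0.06, N = 262, 400 recruited with 34% loss allowed (2.9.1). No correlation between the outcomes is given, so a range is assumed below.

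**Method.** With two groups and two outcomes the global MANOVA test is an F test with df1 = 2, df2 = N − 3 and noncentrality λ = N·f².

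**Step 1: reproduce the plan's figure.** At f² = 0.06 the smallest N with 95% power is 261, or 262 for two equal groups. At N = 262, λ = 262 × 0.06 = 15.72 and power is 95.1%. Other set-ups do not fit: one outcome gives 219, three outcomes 291, and two outcomes at α = 0.025 give 300. The stated calculation is therefore identified and correct.

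**Step 2: the same test at the protocol's own small value.** The ratio is 0.06 / 0.02 = 3.

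| N analysed | λ at f² = 0.02 | Power |
|---|---|---|
| 262 | 5.24 | 51.9% |
| 264 (400 × 0.66) | 5.28 | 52.2% |
| 400 (no information lost) | 8.00 | 71.4% |

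Multiple imputation is planned (2.9.2), so the effective N may exceed 264; the 400 row is the ceiling. At f² = 0.02, 95% power would need 776 analysable patients. With 262, the smallest f² that has 80% power is about 0.038.

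**Step 3: what f² = 0.06 means in SD units.** For two equal groups f² = D²/4, where D is the multivariate (Mahalanobis) distance, so D = 2√0.06 = 0.490.

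- If one of two uncorrelated outcomes moves, d = 0.49 on that outcome.
- If both move equally in the beneficial direction, with correlation r after scoring both so that benefit points the same way, then D² = 2d²/(1 + r) and d = √(2f²(1 + r)). This gives 0.35 at r = 0, 0.39 at r = 0.3 and 0.42 at r = 0.5.

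By the same formulas f² = 0.02 is 2√0.02 = 0.28 on one outcome, or 0.20 to 0.24 on each (r = 0 to 0.5).

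**Step 4: is 0.06 conservative against the cited effects?**

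- PA alone (0.49): 0.49²/4 = 0.060. No discount.
- Depression alone (0.62): 0.62²/4 = 0.096. A discount.
- Both, uncorrelated: (0.62² + 0.49²)/4 = 0.156. At r = 0.5: (0.62² + 0.49² − 2 × 0.5 × 0.62 × 0.49)/(4 × 0.75) = 0.107. A discount in either case.

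**The case against.** The best reply is that nothing has been miscalculated. The article prints 0.06 beside both anchors, so a careful reader can see which effect carries the 95%. The anchors are points, not cut-offs. The target lies inside the assumed small-to-moderate range and is closer to 0.02 (a gap of 0.04) than to 0.15 (a gap of 0.09). It is also well below what the cited depression effect implies. Recruitment is over, no test or decision rule depends on the adjective, and nothing in the article says that a null result will be read as excluding small effects.

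Most of this stands. It removes any charge against N, shows that the claim of conservatism has some basis, and limits the weight of the point. It does not rescue the label. Being nearer to small than to moderate is a reason to say small to moderate, as the same paragraph already does, and power falls from 95% to 52% between 0.06 and 0.02.

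Two stronger readings are tempting, and the document does not support them:

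- **That f² = 0.06 simply is d = 0.49, so nothing was discounted.** This is true only if PA alone moves and the outcomes are uncorrelated. The article expects a medium MADRS effect as well, and against that 0.06 is a discount.
- **That the sample size is wrong or must be enlarged.** The figure of 262 is right for the effect that is printed.

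**Conclusion.** The point holds as a fault in the description, not in the sample size. The design has 95% power for f² = 0.06. For the protocol's own small value it has about 52% with 262 to 264 analysed and no more than 71% with 400. The choice of 0.06 is conservative relative to the cited depression effect or to both effects jointly (f² about 0.11 to 0.16 at assumed correlations of 0.5 to 0). It is not conservative relative to the small anchor or to the cited PA effect taken alone.

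The power figures rest on the two-outcome global F test that reproduces 262 and do not depend on the correlation once f² is fixed. The per-outcome conversions do depend on it, and the range of 0 to 0.5 is an assumption. The severity is minor to moderate: no analysis changes, but the claim affects how a null result would be read.

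**What to change.** In section 2.9.1, or in the report of results now that recruitment has ended, with N unchanged:

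1. Describe f² = 0.06 as small to moderate instead of small.
2. Qualify the claim of conservatism: it holds against the cited depression effect or both cited effects jointly, not against the small anchor or PA alone.
3. State power at f² = 0.02: about 52% with 262 to 264 analysed, with a ceiling of 71% at 400.
4. Say what f² = 0.06 means per outcome: 0.49 SD if one of two uncorrelated outcomes moves, or about 0.35 to 0.42 SD on each if both move equally, naming the assumed correlation.
5. Add that a non-significant MANOVA does not exclude an effect of the protocol's own small size.

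The cost is a few sentences, and a stated power that looks less favourable than it does now.

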#### Statistical analyses

2.9.2

Accelerometer data are analyzed using Actigraph Software ActiLife 6.13.3. Minimal wearing time is eight hours a day, a PA measure of two complete days serving as minimal criteria to count as valid measurement.

Demographic and clinical characteristics of the study population are reported using descriptive statistics. Differences in baseline values between groups are assessed with chi‐squared tests or Fisher's exact test for nominal data and two‐sample *t*‐tests or Mann–Whitney *U* test for metric/ordinal data scales. Missing data will be imputed by multiple imputation techniques.

For assessing group differences in the primary outcome variables depression and PA, MANOVA is done with IBM SPSS Statistics. If baseline group differences occur (e.g., for age, gender, PA baseline level, comorbidity), we adjust for by analysis of covariance (MANCOVA). Furthermore, we report the percentage of participants in each group meeting criteria of WHO‐recommended PA to provide a benchmark to other PA studies. Likewise, we present remission and response rates for PI and TAU, respectively. Additional subgroup analyses are executed if necessary (e.g., concerning trial site, season of data collection, and medication). If MANOVA shows significant results, single ANOVA and discriminant analysis are executed to investigate the relationship between and the influences on the dependent variables.

Secondary data are analyzed by methods appropriate for the respective scale of the parameter and suitable for specific research questions. Results here are of exploratory nature.

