### Study setting

2.2

Selection of these clinics is done due to collaboration in the “Referat für Sportpsychiatrie und –psychotherapie” of the DGPPN including universitary as well as municipal psychiatric clinics in urban and rural areas.

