#### Randomization

2.4.1

Patients are randomly allocated into one of two groups: (1) TAU or (2) TAU plus PI. Randomization—done by a computerized random number generator—is stratified by center with an intended allocation ratio of 1:1. Group assignment is implemented via sequentially numbered, sealed, opaque envelopes. Group allocation is disclosed after baseline measurement.

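### Randomisation is stratified by center, but the stated primary MANOVA has no center term and its adjustment rule would rarely bring one in

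*Protocol article*

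**What the plan says.** Section 2.4.1 (Randomization) says that allocation "is stratified by center with an intended allocation ratio of 1:1", using a computerised random number generator and sealed envelopes. It mentions no blocks.

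Section 2.9.2 (Statistical analyses) gives the primary analysis: "For assessing group differences in the primary outcome variables depression and PA, MANOVA is done with IBM SPSS Statistics". It then sets the rule for covariates: "If baseline group differences occur (e.g., for age, gender, PA baseline level, comorbidity), we adjust for by analysis of covariance (MANCOVA"). Center is not among the examples. Trial site comes up once, further on: "Additional subgroup analyses are executed if necessary (e.g., concerning trial site, season of data collection, and medication"). The Discussion adds, as a strength of the design, only that center effects are open to analysis.

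Section 2.9.1 (Calculation of power and sample size) plans for f² = 0.06 with "5% significance level with a power of 95%) a sample size of 262 is necessary". It enlarges this to 400 randomised: "40 per participating center, enables 34% of data loss by dropout or missing data". At 40 per center, 400 patients imply 10 centers.

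Section 2.2 (Study setting) describes the sites as "universitary as well as municipal psychiatric clinics in urban and rural areas". Section 2.4.2 notes that most, but not all, clinics offer some exercise program within usual care.

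**The concern.** A factor used to stratify the randomisation normally belongs in the primary model. Here the text works against that. Adjustment is triggered by an observed baseline difference between arms, and stratification exists to prevent such a difference in center. Followed as written, the plan would leave out of the model the one factor that the design controls.

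Center could plausibly matter for both primary outcomes. The clinics differ in type and location, and the exercise offered within usual care bears directly on step counts. When the arms are balanced within center, variation between centers drops out of the treatment contrast. A model without center still counts that variation as residual error. The reported standard error is then larger than the true one, and the test rejects less often than its nominal level. What is at stake is precision and some power, not bias.

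**Working it through.** **Inputs from the article.** Two arms; two primary outcomes (MADRS and mean steps); alpha 5%; power 95%; f² = 0.06; 262 evaluable; 34% data loss; 400 randomised; 40 per center.

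**Input not in the article.** The between-center ICC. It is assumed to be the same for both outcomes and is varied from 0 to 0.20.

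**Step 1: the plan's own figure.** For a two-group MANOVA with two outcomes, the test is an F with df1 = 2, df2 = N − 3 and noncentrality N × f².
- The smallest N with 95% power is 261 (power 95.05%). N = 262 gives 95.1%, so the stated 262 reproduces.
- Inflation gives 262 / (1 − 0.34) = 397, against 396 before rounding to 400. The difference is immaterial.
- This calculation contains no center term.

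**Step 2: approximate effect under balance within center.** With total variance 1, the group contrast carries only the within-center share, 1 − ICC, while the model without center uses the full variance.
- Reported SE divided by true SE = 1/√(1 − ICC).
- In large samples the two-outcome statistic is (1 − ICC) times a chi-square on 2 df. A chi-square on 2 df exceeds x with probability exp(−x/2), so the actual type I error is 0.05^(1/(1 − ICC)).

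| Assumed ICC | SE ratio | Exponent 1/(1 − ICC) | Approximate type I error |
|---|---|---|---|
| 0.02 | 1.010 | 1.020 | 4.7% |
| 0.05 | 1.026 | 1.053 | 4.3% |
| 0.10 | 1.054 | 1.111 | 3.6% |
| 0.15 | 1.085 | 1.176 | 2.9% |

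**Step 3: simulation.** 10 centers of 26 evaluable patients (260 in all), two outcomes, exact F test for group with and without center as a fixed factor. There were 5000 null runs and 3000 runs at f² = 0.06 for each ICC. Allocation was balanced 1:1 within center.

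| ICC | Type I error without / with center | Power without / with center |
|---|---|---|
| 0 | 5.2% / 5.2% | 95.1% / 95.2% |
| 0.02 | 4.1% / 4.4% | 95.2% / 95.3% |
| 0.05 | 4.8% / 5.3% | 95.2% / 95.5% |
| 0.10 | 4.1% / 5.1% | 95.9% / 96.8% |
| 0.20 | 2.6% / 4.5% | 96.6% / 98.1% |

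The Monte Carlo standard error of the type I error is about 0.3 percentage points. Up to ICC 0.05 the effect is within or near that noise; from about 0.10 it is clear.

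**Step 4: the same simulation with simple randomisation within center.** The test without center kept a type I error of 4.8% to 5.1% at every ICC. The conservatism therefore comes from balance within center, not from the missing term alone. What remains under simple randomisation is lost efficiency.

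**Step 5: cost of the term.** Ten centers use 9 degrees of freedom. With N = 262, df2 falls from 259 to 259 − 9 = 250.

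**The case against.** The strongest reply is that a condensed article need not list every model term, that the analysis plan is not shown, and that the covariate examples are open-ended. The article also names trial site for further analysis. This would carry more weight if the text were merely silent. It is not: it states the rule by which covariates enter, and that rule would rarely admit a stratified factor. A site subgroup analysis asks whether the effect differs between centers, which is not the same as putting center in the primary model.

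Three other objections stand and limit the point.
- **Balance within center is not stated.** The figure of 40 per center is a recruitment target, not a statement about balance between arms. Stratification with an intended 1:1 ratio usually implies blocks, but the article does not say so. Even with blocks, the 34% data loss allowed for could upset balance among evaluable patients.
- **The ICC is unknown.** The settings differ, but nothing in the article shows how far outcomes differ between them.
- **The loss is small.** Planned power is met in every simulated scenario.

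A reader might infer that the true type I error is certainly below 5%, or that the stratification is wasted. The article supports neither. The first depends on the two unstated conditions above. The second is wrong: under exact balance the estimated group difference is the same with or without center and keeps its precision, and only the reported standard error fails to reflect it.

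**Conclusion.** The point holds as a conditional loss of efficiency. The primary analysis, as written, leaves out the stratification factor, and the stated adjustment rule is unlikely to restore it. If allocation is balanced within center and outcomes vary by center, the test is mildly conservative: about 4.3% at an assumed ICC of 5% and 3.6% at 10%, taking one ICC for both outcomes. If allocation within center is simple, the level is about right and only efficiency is lost. At the planned effect, the simulated power given up is 96.8 − 95.9 = 0.9 points at ICC 0.10 and 98.1 − 96.6 = 1.5 points at ICC 0.20.

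It should not be read as a threat to validity or as evidence of an underpowered trial. The error is not in the anti-conservative direction, and the sample size stands. The case for change is that the better analysis costs almost nothing.

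**What to change.** Prespecify center as a fixed factor in the primary MANOVA or MANCOVA, and in the follow-up single-outcome ANOVAs, whatever the baseline comparisons show. Keep treatment-by-center as an exploratory analysis. State whether allocation was blocked within center, so that the reader can tell which of the two cases applies.

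The cost is a change of wording and about 9 error degrees of freedom. The sample size of 262 evaluable and 400 randomised is unchanged, and no new data are needed. The article reports that recruitment has finished, so the change should be documented before the arms are compared.

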### Data collection

2.6

Table 1 displays all measurements at different points in time line. All questionnaires are administered in German language.

**TABLE 1 mpr1862-tbl-0001:** Time table of measurements

		T0 (baseline)	T1a (4 weeks)	T1b (discharge)	T2 (follow‐up)
Physical activity					
Objective	Accelerometer measurement for 3 days (primary outcome)	x	x	x	x
Subjective	**Q:** IPAQ short version (7)	x	x	x	x
Adherence	**AD:** Copy of step protocols (IG only)	‐	x	x	x
Depression					
Objective	**I:** Montgomery–Åsberg Depression Rating Scale (primary outcome) (10)	x	x	x	x
Subjective	**Q:** Beck‐Depression‐Inventory II (21)	x	x	x	x
General, physical, and clinical measures					
General measures	**Q:** Sociodemographic data, medication	x	‐	‐	‐
Physiological measures	**HR:** Blood pressure, heart rate, weight, and blood glucose	x	‐	‐	‐
Laboratory values	**HR:** Triglycerides, cholesterol, high density lipoprotein, low density lipoprotein	x	‐	‐	‐
Clinical history	**Q:** Anamnestic questions (6)	x	‐	‐	‐
Psychiatric symptoms	**Q:** Symptom checklist 27 (27)	x	x	x	x
Anxiety	**Q:** Beck anxiety inventory (21)	x	x	x	x
General health quality	**Q:** Short‐Form Health‐Survey 12 (12)	x	x	x	x
Intervention evaluation	**Q:** Questions about the implementation of PI (5)	‐	‐	‐	x
Treatment history	**Q:** Concomitant treatment since discharge (13)	‐	‐	‐	x
Critical life events	**Q:** Social Readjustment Rating Scale (43)	‐	‐	‐	x
Components of the MoVo‐model					
Intention, motivation and volition	**Q:** Intention (2), physical activity specific self‐efficacy (6), outcome expectancies (6), self‐concordance scale (12), action planning (4), coping planning (4)	x	x	x	x

Abbreviations: ( ), number of items; AD, activity diary; HR, information out of hospital record; I, interview; IPAQ, International Physical Activity Questionnaire; MoVo‐Model, Motivation Volition Process Model; PI, pedometer intervention; Q, Online‐Questionnaire or Paper/Pencil.

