First, we measure PA objectively (with some constraints: some types of PA cannot be registered correctly or at all like climbing or swimming and wear time cannot be controlled) and subjectively and provide an assessment of depression severity by blinded raters as well as subjectively reported depressive symptomsSecond, the population is generalizable, for being recruited in a naturalistic clinic field in different study centers. Center effects can be analyzedThird, we will provide follow‐up dataFourth, a unique aspect of our PA intervention is that it is personalized and adaptive concerning intensity, length, frequency, and personal circumstances and that is developed based on an empirically supported psychological background. Patients can execute it and continue it afterward in self‐managementFifth, we take into account the effect of comorbid anxiety on our results

Our findings will contribute to the research field of exercise and depression in severely depressed patients and results will give opportunity for refining exercise‐related interventions in inpatient care.

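### Baseline MADRS and baseline steps enter the primary model only if a baseline test happens to show a group difference, which costs efficiency and leaves the covariate set to chance

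*Protocol article*

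**What the plan says.** Section 2.9.2 (Statistical analyses) names the primary test: "For assessing group differences in the primary outcome variables depression and PA, MANOVA is done with IBM SPSS Statistics". No baseline term, time factor or change score is stated for it. Just before that, the section sets up between-group baseline testing: "Differences in baseline values between groups are assessed with" chi-squared, Fisher, t- or Mann-Whitney tests, with no significance threshold given. Adjustment then depends on the result: "If baseline group differences occur (e.g., for age, gender, PA baseline level, comorbidity), we adjust for by analysis of covariance (MANCOVA". The baseline of one primary outcome, physical activity, is therefore itself a conditional covariate. Baseline MADRS is not named, although the list is only illustrative. If the MANOVA is significant, single ANOVAs and a discriminant analysis follow.

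Both baselines are scheduled. Table 1 in section 2.6 lists "Accelerometer measurement for 3 days (primary outcome") and the MADRS at T0, T1a, T1b and T2. Section 2.4.1 says that allocation is revealed only after the baseline measurement, that allocation is stratified by center, and that it is made "with an intended allocation ratio of 1:1". Section 2.9.1 sizes the trial for the MANOVA: "5% significance level with a power of 95%) a sample size of 262 is necessary", at f² = 0.06.

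**The concern.** In a properly randomised trial, any baseline difference between arms is due to chance. A test of that difference does not address the question that matters for adjustment, which is whether the variable predicts the outcome. The baseline value of an outcome is commonly its best available predictor. It is worth including whether or not the arms differ on it.

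Two things are at stake. The first is efficiency: in most realisations of the trial, two scheduled and plausibly prognostic measurements would be left out of the primary test. The second is pre-specification: which covariates enter depends on the observed baseline data, on an open-ended list and on an unstated threshold. Two analysts could apply the rule to the same data and fit different primary models.

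**Working it through.** **Inputs from the article.** Two groups, 1:1 (2.4.1); two primary outcomes (2.9.2); f² = 0.06, alpha 5%, power 95%, N = 262 (2.9.1).

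**Assumptions.** The baseline-outcome correlation r is not given. It is taken as 0.3 to 0.6 and equal for both outcomes (0.7 appears in one simulation as an extreme). The baseline tests are taken as two-sided at 5% and independent.

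**Step 1: reproduce 262.** For p = 2 outcomes and g = 2 groups, the global test is an F test with df1 = p(g − 1) = 2, df2 = N − g − p + 1 = N − 3 and noncentrality λ = N·f². At N = 262, df2 = 259 and λ = 262 × 0.06 = 15.72, which gives power 95.1%. The smallest N is 261, or 262 with equal arms. One outcome would need 220 and three would need 292. The stated figure is thus the two-outcome MANOVA, with no credit taken for baseline information.

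**Step 2: how often the baselines are used.** The chance that at least one of the two baseline tests is significant is 1 − 0.95² = 9.75% (simulated: 9-10%). Neither baseline enters in 0.95² = 90.25% of trials.

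**Step 3: what always adjusting gains.** If each baseline explains r² of its outcome's variance, the effect size becomes f²/(1 − r²), and two covariates reduce df2 to N − 5 = 257.

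| r | f² = 0.06 becomes | power at 262 | N for 95% power | f² = 0.03 becomes | power at 262 |
|---|---|---|---|---|---|
| unadjusted | 0.0600 | 95.1% | 262 | 0.0300 | 70.4% |
| 0.3 | 0.0659 | 96.7% | 238 | 0.0330 | 74.7% |
| 0.4 | 0.0714 | 97.8% | 220 | 0.0357 | 78.3% |
| 0.5 | 0.0800 | 98.8% | 198 | 0.0400 | 83.0% |
| 0.6 | 0.0938 | 99.6% | 168 | 0.0469 | 88.7% |

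The value f² = 0.03 is half the design effect. It is shown to indicate what happens if the true effect is smaller than planned.

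**Step 4: how much the conditional rule recovers.** This was simulated for the two-outcome MANOVA with 131 per arm, independent outcomes and 6000 trials per setting. Power is given as never / conditional / always adjusting.

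- f² = 0.03: 70.2 / 70.6 / 74.4% at r = 0.3; 70.6 / 71.4 / 83.4% at r = 0.5; 70.0 / 71.7 / 94.4% at r = 0.7.
- f² = 0.06: 95.0 / 95.0 / 96.5%; 95.3 / 95.9 / 98.8%; 94.8 / 95.9 / 99.9% at the same values of r.

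The conditional rule performs almost like never adjusting.

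**Step 5: type I error.** Under the null, the conditional rule rejected in 4.6% (r = 0.3), 3.9% (r = 0.5) and 3.3% (r = 0.7) of simulated trials, against about 5% for always adjusting. The rule is conservative.

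**The case against.** The strongest defence is that nothing promised is broken. The 262 was computed without covariates, so the stated 95% power at f² = 0.06 does not depend on adjustment. The rule is written down in advance and reacts only to pre-treatment data, never to outcomes. This stands, and it limits the point to efficiency and to a loosely specified covariate set.

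Four stronger readings are tempting but not supported.

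- *The trial is underpowered.* A calculation on one outcome at d = 0.35 gives power near 81% and a larger gain from adjusting. Two independent outcomes at d = 0.35 give f² = 2 × 0.35²/4 = 0.061, so that calculation tests one component of the planned joint effect. It is not the primary test.
- *The rule inflates false positives.* For a single outcome at r = 0.6, the rejection rate is about 10% in the roughly 14% of trials whose baseline imbalance is sizeable but not significant (|z| 1.3 to 1.96). That rate is conditional on the imbalance; over all trials the error is below 5%.
- *The Discussion's claim on anxiety is contradicted.* The sentence "we take into account the effect of comorbid anxiety on our results" does not promise covariate adjustment in the primary model. Anxiety is measured at all four time points and is a secondary objective.
- *Every patient has usable baseline values.* Baseline steps are scheduled for all, but a valid measurement needs two days of at least eight hours, and section 2.9.1 budgets for accelerometer data loss. Some values will need imputing.

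Two further reservations affect the size. Sections 1.5.2 and 1.5.3 speak of change from admission, so change scores cannot be excluded, although section 2.9.1 frames the expected effects as differences at discharge. With change scores the gains in the table would not apply as they stand. Adjustment would still be no less precise: with equal variances, the ratio of residual variances is (1 − r²)/[2(1 − r)] = (1 + r)/2, which is below 1. Also, excluding patients above 10,000 baseline steps restricts the range and may lower r for steps.

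**Conclusion.** The point holds as one of efficiency and pre-specification; the primary test remains valid. The trigger selects covariates by chance imbalance, not by prognostic value. It leaves both outcome baselines out in about 90% of trials and recovers almost none of the available gain. At the design effect that gain is modest, 1.6 to 4.5 percentage points for r = 0.3 to 0.6. At half that effect it is 4.3 to 18.3 points (74.7 − 70.4 and 88.7 − 70.4). These sizes rest on an assumed r common to both outcomes, on final values being analysed, and on N = 262 evaluable patients. The 90% figure rests on an assumed 5% threshold and on independent tests. The direction of the conclusion does not depend on the exact r, provided the baselines predict their outcomes at all.

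**What to change.** Delete the clause that makes adjustment depend on observed baseline differences, together with the baseline significance tests, and report baseline data descriptively. Before unblinding, fix the primary model as a MANCOVA of MADRS and mean daily steps on treatment. It should always contain baseline MADRS, baseline mean steps and centre, the last because randomisation was stratified by it. Use the same terms in the single-outcome follow-up models. Handle missing baseline steps within the multiple imputation already planned.

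No new data are needed. The two baseline covariates take the error degrees of freedom from 259 to 257 at N = 262. If the 400 patients at 40 per centre mean 10 centres, entering centre as a factor takes a further 9, leaving 248.
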